##### Analyses of secondary endpoints

Secondary outcomes will be analyzed using either mixed models for repeated measures (heterogeneous first-order autoregressive structured covariance matrix over time) or generalized estimating equation approaches with corresponding marginal means and contrast tests (multilevel modeling). Time-to-dropout distributions will be summarized by the Kaplan–Meier method and compared using the (stratified) log-rank test. All efficacy variables will be summarized by time point and treatment arm (mean, standard deviation, percentiles (i.e., minimum, 25^th^, 50^th^, 75^th^, and maximum), count, percentage). Moreover, moderation, mediation and conditional process modeling [80] will be conducted based on regression and structural equations (interaction, simple slope analysis; direct/indirect effects, kappa squared).

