##### Mediators of change

As one potential mediator, (1) treatment fidelity will be assessed using an adapted version of the THAV Integrity Questionnaire [71] and the ScouT Treatment Integrity Questionnaire [72], which measure treatment integrity throughout the whole treatment process. After each unit of THAV/ ScouT therapy, the therapist will record the percentage of time he/she spent implementing the specific therapy elements from the THAV or ScouT program. In addition, the therapist will document which materials (e.g., worksheets, therapeutic stories, etc.) were used during the treatment sessions. The THAV Integrity Questionnaire has shown satisfactory reliability scores [13] and the ScouT Treatment Integrity Questionnaire has shown excellent internal consistencies [14]. Moreover, as a possible mediator, we will measure the (2) therapist-patient relationship and therapist-caregiver relationship using the German Relationship Questionnaire for Child and Adolescent Psychotherapy (BeKi) [73]. In order to assess each alliance from the perspectives of both parties, the BeKi has four separate versions: two for the therapist evaluating his/her alliance to the patient (BeKi therapist-patient) or parent (BeKi therapist-parent), and one each for the patient (BeKi patient) and the parent (BeKi parent) evaluating their respective alliances to the therapist.

(3) Moreover, we will assess the parent rating of adaptive and maladaptive emotion regulation strategies (FRUST parents, see above) [51].

(4) Additionally, after every therapy session, we will assess treatment adherence as a mediator using the Adherence Questionnaire. Four different items will be used to operationalize adherence as the child’s cooperation during the therapy session and adherence as the implementation of therapy homework. For this study, a modified version of the Adherence Questionnaire [42] will be used. Internal consistencies of the original Adherence Questionnaire range between α ≥ 0.95 or α ≥ 0.95 for children and α ≥ 0.97 or α ≥ 0.97 for parents [13, 14].

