#### Sample size

A total number of 70 children 35 / 35 between the ages of 6;0 and 12;11 will be included in this exploratory study. To date, the effects of smartphone-augmented CBT on the implementation of therapy homework in children with aggressive behavior have barely been investigated. Other explanatory studies refer to an even a smaller number of cases [15, 23]. As the AUTHARK study aims to provide a basis for preparing a subsequent multicenter trial, the sample size needed is not based on formal power calculations. Instead, a sample size is proposed that allows us to precisely estimate the variance of critical outcome parameters that can then be entered into a power calculation for a confirmatory trial. In this way, the overall sample size for the main RCT can be minimized [74].

Based on results from the previous literature, we assume a small to moderate effect size (Cohen’s d ~ 0.4) [75], for which approximately 30 participants per treatment arm for a pilot randomized trial are recommended [74, 76]. Furthermore, a study with a similar design, comparing two groups across four assessment points (pre-, post-, and follow-up measurements), expects moderate effects regarding the app’s influence on therapy homework with a sample size of *n* = 35 per group [16]. Moreover, the power of a sample can be increased by a high number of measurements per patient [77]. In our study, THA will be measured at least eight times over a period of approximately sixteen weeks. At each assessment, the patients will be asked to use the smartphone app for five consecutive schooldays. Based on previous trials with a similar patient population and interventions, a dropout rate between 10 and 15% is expected [78]. Therefore, *n* = 35 patients per group (total: *n* = 70) should be recruited.

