## Discussion

The AUTHARK study will yield information about the effects of smartphone-augmented CBT on the THA compared to conventional paper-and-pencil assignments completed between therapy sessions for children aged 6–12 years with a diagnosis of ODD/CD.

The study will also explore the role of therapy homework as a possible mediator of treatment outcome. Furthermore, the trial will describe possible effects of app-augmented CBT on the symptoms of ODD / CD, ADHD, and other comorbid behavioral or emotional problems; on individually defined problem behaviors; on triggering and maintaining factors of peer- and adult-related aggression (social cognitive information processing, impulse control, social skills, empathy, adaptive and maladaptive strategies for regulation of emotions, problem solving competences); on the children’s quality of life; on the children’s and parents’/caregivers’ level of psychosocial functioning; and on the parents’/caregivers’ and patients’ satisfaction with the treatment.

Since this study is designed as a pilot study, there are some aspects that may prove challenging during the course of the study. One of these aspects is the young age of the children we plan to include. However, our preliminary experience with children in this age range is that even children aged six to seven years are able to handle the smartphones and the requirements of the app. This experience is also supported by the results of a small pilot study that investigated the use of a language app with kindergarten children. The authors reported that children aged three to five years were able to use the app well with support [81]. Moreover, the effects of age on usability and adherence to the intervention will be analyzed.

Another challenge of the study is the risk of bias regarding the outcome ratings. Although participating families will not be informed about the hypotheses of the study, they may conclude from the information letter that the use of the AUTHARK app is an innovation and is expected to result in higher therapy homework adherence. Likewise, the treating therapists cannot be blinded to the intervention. However, the detailed descriptions of quality criteria, on which the rating is based, (see “15”) may reduce the risk of bias. Moreover, in a subsequent main study, an independent blinded evaluation of therapy homework adherence will be considered.

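### Kappa squared, the only mediation effect-size index named, does not measure a share of the largest possible indirect effect

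*Protocol article*

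**What the plan says.** Under Analyses of secondary endpoints the article states: "Moreover, moderation, mediation and conditional process modeling [80] will be conducted based on regression and structural equations". The bracket that follows names the quantities: "interaction, simple slope analysis; direct/indirect effects, kappa squared". Next to direct and indirect effects, kappa squared can only be the mediation effect size. The article gives no formula for it, no reading of it and no other index.

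Mediators of change lists treatment fidelity, the therapeutic relationship, parent-rated emotion regulation and adherence. On the last it says: "we will assess treatment adherence as a mediator using the Adherence Questionnaire". The Discussion gives the aim: "The study will also explore the role of therapy homework as a possible mediator of treatment outcome".

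**The concern.** Kappa squared is meant to say how large an indirect effect is relative to the largest one that could have occurred. That reading needs a denominator that is a maximum. The denominator multiplies a limit for a and a limit for b, each derived with different quantities held fixed, and the two limits do not belong to one common situation. If the product is not a maximum, a statement such as 'mediation reached 9% of what was possible' has no basis. Nothing in the output would reveal this, because the value looks like an ordinary proportion. At stake is how readers interpret the exploratory mediation results.

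**Working it through.** **Inputs.** The article gives no path coefficients and no formula, so there is no figure to reproduce. Two things are assumed: the standard definition of kappa squared for X → M → Y with standardised variables (X the arm, M the mediator, Y the outcome), and illustrative correlations.

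**Definition.** With a = r_XM and b = (r_YM − r_XM·r_XY)/(1 − r_XM²):

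- M(a) = r_YM·r_XY + √[(1 − r_YM²)(1 − r_XY²)], the limit of a with r_YM and r_XY fixed
- M(b) = √[(1 − r_XY²)/(1 − a²)], the limit of b with r_XY and the observed a fixed
- kappa squared = ab / [M(a)·M(b)]

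**Example:** a = b = 0.3, total effect r_XY = 0.2.

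- Direct effect c′ = 0.2 − 0.09 = 0.11
- r_YM = b + c′a = 0.3 + 0.11 × 0.3 = 0.333
- M(a) = 0.333 × 0.2 + √[(1 − 0.333²)(0.96)] = 0.990
- M(b) = √(0.96/0.91) = 1.027
- Denominator = 1.017; kappa squared = 0.09/1.017 = 0.088

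**Is 1.017 a maximum? Same r_XY and r_YM.** Then ab = a(0.333 − 0.2a)/(1 − a²):

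| a | ab |
|---|---|
| 0.50 | 0.155 |
| 0.80 | 0.384 |
| 0.90 | 0.725 |
| 0.93 | 1.012 |
| 0.95 | 1.393 |

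The correlation matrix is positive definite at every row. The stated maximum is passed just above a = 0.93.

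**Only r_XY fixed.** The largest b at a given a is √[0.96/(1 − a²)], so ab can approach a·√[0.96/(1 − a²)]. This is 1.31 at a = 0.80 and 2.02 at a = 0.90, and it grows without bound as a approaches 1. No finite maximum exists that could replace the denominator.

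**How far is the number from the plain indirect effect?** In the example it is 0.088 against a fully standardised ab of 0.090. Over 20,000 draws with all three correlations between 0.1 and 0.5, the Spearman correlation between kappa squared and standardised ab is 0.998.

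**Equal indirect effects, total effect 0.2, ab = 0.10 in both cases:**

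- a = 0.2, b = 0.5: r_YM = 0.52, M(a) = 0.941, M(b) = 1.000, kappa squared = 0.10/0.941 = 0.106
- a = 0.5, b = 0.2: r_YM = 0.25, M(a) = 0.999, M(b) = 1.131, kappa squared = 0.10/1.130 = 0.089

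**The case against.** The strongest reply is that the defect has little numerical effect here. The denominator is exceeded only at values of a that this trial will not see. With 1:1 arms, a = 0.93 is a mediator difference of 2 × 0.93/√(1 − 0.93²) ≈ 5.1 within-arm SDs, while the Sample size section assumes d of about 0.4. At modest correlations the index nearly equals standardised ab and ranks mediators almost identically. In 137,900 random valid correlation matrices the observed ab never exceeded its own denominator. The article never calls the index a share of a maximum. It also already plans the indirect effect itself and foresees a separate analysis plan for details.

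Most of this stands, and it limits the point to the meaning of the index. It does not rescue the index: a quantity close to standardised ab adds nothing to it, and the one property that would set it apart does not hold. The definition of kappa squared is not in the article. It is assumed here, and the algebra that follows can be checked from it.

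A reader might infer four stronger things, none of which is supported:

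- *The denominator is too small by a fixed, large factor.* At a = 0.99 in the example ab is 6.72, about 6.6 times 1.017. That ratio belongs to an unrealistic a and changes with which correlations are held fixed.
- *A two-level arm variable makes the limits unattainable.* This depends on the distributions of mediator and outcome, and the argument does not need it.
- *Values cannot be compared across mediators.* Equal indirect effects can differ somewhat (0.106 against 0.089), but the near-identical ranking contradicts a general claim.
- *Planning of the multicentre trial is compromised.* The Sample size section says the pilot informs that trial through the variance of critical outcome parameters. It does not mention mediation effect sizes.

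**Conclusion.** The point holds as a minor one. The article fixes an index whose denominator is not the maximum possible indirect effect, so its value is not a proportion of that maximum. This follows from the standard definition whatever the trial's correlations turn out to be; only the illustrative figures are assumed. The numerical consequence at modest correlations is small: 0.088 against 0.090 in the example, with some unevenness between mediators that have the same ab. An unseen analysis plan could add detail, but the article itself names the index.

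Mediation is an exploratory secondary analysis here. The primary endpoint, the sample size (of which the article says "the sample size needed is not based on formal power calculations") and the direct and indirect effects named in the same bracket are unaffected.

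**What to change.** In Analyses of secondary endpoints, delete kappa squared from the bracket and keep the direct and indirect effects. State that each indirect effect will be reported on the outcome scale and, because the arm is binary, partially standardised (divided by the outcome SD), both with a percentile bootstrap 95% confidence interval.

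The cost is one phrase. The planned mediation models already yield these quantities, and no data collection, sample size or primary analysis changes.

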##### Missing values

It should be emphasized that as few patients as possible should discontinue treatment and that all patients should be followed up and documented after discontinuation of the treatment in order to record data required according to the ITT principle. To assess the impact of up to 20% attrition, multiple imputation approaches will be taken, accounting for proxy measures and assuming specific missingness-not-at-random patterns. Sensitivity analysis with a data set with and without imputation will be computed to assess the effects of missing values. The details will be documented in a statistical analysis plan. The analysis of subjects essentially observed and treated per protocol is supportive.

#### Stopping rules

##### Stopping rules for an individual patient

One (or more) of the following circumstances will result in an early study termination of single subjects (these trial subjects will be rated as dropouts): (i) withdrawal of informed consent of one parent (in the case of joint custody)/caregiver/guardian; (ii) withdrawal of assent of the patient; (iii) unwillingness to further participate in the trial; (iv) need for inpatient treatment or other reasons affecting the patient’s well-being in the case of continued trial participation; (v) need for a different kind of treatment for health reasons according to the judgment of the attending physician.

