## Methods

### Trial design

The AUTHARK study is designed as an interventional randomized controlled study with two parallel treatment arms.

Figure 1 shows the overall design of the AUTHARK study. After the initial screening at T1, patients who meet the inclusion criteria will be randomly assigned to one of the treatment arms. Children in both the experimental group and the control group will receive social skills training (combination of THAV [4] and ScouT [7]). In addition to the treatment, the AUHARK smartphone app will be used in the experimental group. The treatment will be administered in three phases (1–3). Each phase includes eight weekly therapy sessions with the children and two to three sessions with the parents/caregivers. The first treatment phase (1) is followed by an intermediate assessment (T2) with a reduced set of assessment instruments. The second treatment phase (2) is followed by a major assessment (T3). Children who no longer show clinically significant symptoms of ODD/CD at T3 will not receive further therapy but will participate in a first follow-up assessment (T4) eight weeks after T3. Those patients with significant symptoms at T3 will undergo a third treatment phase with a further eight child sessions and two to three caregiver sessions, which will be followed by the T4 assessment. A follow-up evaluation (T5) for all patients will take place one year after T4.

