### Recruitment, inclusion and exclusion criteria

Patients for the AUTHARK study will be recruited from three different sites: (1) the outpatient units of the Department of Child and Adolescent Psychiatry and of the School of Child and Adolescent Behaviour Therapy (AKiP) at the University Hospital Cologne, (2) primary and special education schools and (3) pediatric and psychiatric practices in Cologne, Germany.

Participants will be included if they meet the following inclusion criteria: (1) child age: 6;0 to 12;11 years at T1; (2) clinician-rated diagnosis of ODD/CD based on a structured interview (ILF-EXTERNAL) that is part of the comprehensive Structured Interview for Children and Adolescents according to ICD-10 and DSM-5 from the DISYPS Systems (DISYPS- ILF) [53] at T1; (3) parent-rated ODD/CD symptoms from the parent-rated DISYPS III Symptom Checklist for Disruptive Behaviour Disorder (SCL-DBD parent) [43] with a stanine score of 7 or higher at T1; (4) peer-related aggressive (verbal and/or physical) behavior must be reported by the parents/caregivers at T1; (5) willingness and ability (e.g. sufficient knowledge of German, sufficient competence in using a smartphone) of patient and parents/caregivers to participate in the intervention; (6) children treated with a stable dose of psychotropic medication (e.g. methylphenidate) will be included in the trial. Criteria (2) and (3) will also be evaluated again at T3. If these two criteria no longer apply to the patients at T3, the study participation will be terminated.

The following exclusion criteria will be applied and evaluated at T1: (1) child’s intelligence is below average (IQ < 85) based on a standard intelligence test (German version of the Culture Fair Intelligence Test, Primary Intelligence Scale 1 (CFT 1-R) [54] and Scale 2 (CFT 20-R) [55]; (2) Autism spectrum disorder or other severe comorbid disorder which dominates the clinical picture according to clinical rating; (3) Current or planned inpatient psychotherapy or outpatient behavioral parent management training on a weekly/biweekly basis; (4) Low level of German language skills of the patient or the parents/caregivers.

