#### Participant timeline

The individual study duration per patient is between five and seven months. Measurements will take place according to a specific schedule. The trial consists of three general parts: a screening process, the intervention period, and the follow-up assessment. Through an initial investigation using standardized telephone screening, a broad assessment of the inclusion and exclusion criteria will be conducted. Shortly after this initial investigation, the pre-treatment measurement (T1) will occur, which involves a detailed examination of the inclusion and exclusion criteria. After being randomized to the experimental or control group, all patients will undergo a first treatment phase (1), consisting of eight patient sessions and two to three parent/caregiver sessions, followed by an intermediate assessment (T2). Subsequently, another treatment phase (2) will be carried out, followed by a main assessment (T3). Non-responders to the treatment (significant symptoms of OD/CDD at T3 based on the clinician-rated parent interview (ILF-EXTERNAL) [53] and on the parent rating (SCL-DBD) from the DISYPS-III [43]) will participate in a third treatment phase (3), followed by a final assessment (T4). Responders to the treatment (no significant symptoms of ODD/CD at T3) will terminate the study and take part in a first follow-up assessment (T3) eight weeks after their last session. After one year, every family will be asked to complete a follow-up survey (T5).

Therefore, four study visits (T1-T4) will take place for all children and parents/caregivers in order to complete assessments. Additionally, there will be 16 study visits for all children and four to six study visits for all parents/caregivers (treatment phases 1 and 2). Within the group of non-responders after T3, there will be a further eight visits for children and two to three visits for parents/caregivers (treatment phase 3).

At the main assessment points (T1, T3/T4), the primary outcome (THA) and the secondary outcomes will be assessed. At the intermediate assessment (T2), the primary outcome and symptoms of ODD/CD as well as comorbid conditions will be assessed using only parent- and child-report questionnaires and without a clinical interview. The primary outcome will additionally be assessed every two weeks, as the therapist will rate the children’s THA using the Adherence Questionnaire (Fig. 5).

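### The individual stopping rule puts inpatient need and a change of treatment under study termination, on the same terms as withdrawn consent, and does not say that assessments continue

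*Protocol article*

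**What the plan says.** **Stopping rules for an individual patient.** Five circumstances each "will result in an early study termination of single subjects (these trial subjects will be rated as dropouts"). Reasons (i) to (iii) are withdrawal of consent, withdrawal of the child's assent, and unwillingness to continue. Reason (iv) joins need for inpatient treatment with other grounds touching the child's well-being if the trial continues. Reason (v) is "need for a different kind of treatment for health reasons according to the judgment of the attending physician". All five carry the same consequence and the same label.

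**Missing values.** The section states that "all patients should be followed up and documented after discontinuation of the treatment in order to record data required according to the ITT principle".

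**Trial design and Participant timeline.** "A follow-up evaluation (T5) for all patients will take place one year after T4", and "every family will be asked to complete a follow-up survey (T5"). The timeline also counts the four visits T1 to T4 for all children and caregivers.

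**Responders.** The eligibility section says of children who no longer meet the symptom criteria: "If these two criteria no longer apply to the patients at T3, the study participation will be terminated". The Participant timeline says that responders "will terminate the study and take part in a first follow-up assessment (T3) eight weeks after their last session"; Trial design calls that follow-up visit T4.

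**Analyses of primary endpoint.** The full analysis set is intention-to-treat: every randomized child with a valid baseline.

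**The concern.** Stopping the study treatment and leaving the study are different events. Reasons (i) to (iii) properly end data collection. A child who needs a ward or another therapy has stopped the trial treatment, but the family may still be willing to fill in questionnaires. The stopping rule does not make this distinction. It is phrased as something that will happen, whereas the follow-up sentence under Missing values is phrased as something that should happen. Staff holding both could reasonably act on the stopping rule and cease to request assessments.

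The children concerned may well be among those doing worst, although the document does not say so, and (v) covers any other treatment given for health reasons. They stay in the intention-to-treat set, so their missing values would be imputed when some could have been collected. What is lost would then be related to outcome, and avoidably so.

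**Working it through.** **1. The plan's own figure.** The concern disputes no number, but the dropout allowance gives the scale. The Sample size section starts from about 30 per arm and expects 10 to 15% dropout.

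- 30 / (1 − 0.10) = 33.3, rounded up to 34
- 30 / (1 − 0.15) = 35.3, rounded up to 36

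The stated 35 per arm fits. Dropout for all reasons is then 0.10 × 70 = 7 to 0.15 × 70 = 10.5 children. No share is given for inpatient need or (v). Planned inpatient psychotherapy is an exclusion criterion, so few such exits are likely.

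**2. The texts side by side.**

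| Group | Wording on leaving | Are later assessments stated? |
|---|---|---|
| Responders at T3 | Participation terminated | Yes, specifically: the eight-week follow-up, then T5 |
| (i) to (iii) | Study termination, dropout | Consent, assent or willingness is gone, so assessments end |
| Inpatient need in (iv), and (v) | Study termination, dropout | Only through the general statements on all patients and every family |

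For responders, the apparent end of participation is corrected by an explicit visit plan. For the clinical exits, the general statements point towards follow-up, but nothing in the stopping rule repeats or refers to them.

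**3. What is still outstanding when such a child stops.**

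- T2: the protocol says "symptoms of ODD/CD as well as comorbid conditions will be assessed using only parent- and child-report questionnaires".
- T3/T4: the fuller secondary and supplementary set, including functioning and quality of life.
- T5: the one-year survey.
- Therapy homework adherence: nothing, because no homework is set after therapy ends.

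**4. An illustration of scale on assumed inputs.** The document supplies none of the following: 0 to 2 more exits in one arm of 35 than in the other, and leavers ending G = 1.0 to 1.5 SD worse than stayers.

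Observed-data bias = (difference in exit share) × G.

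- 0 extra exits: 0
- 1 extra: 1/35 = 0.029, giving 0.029 to 0.043 SD
- 2 extra: 2/35 = 0.057, giving 0.057 to 0.086 SD

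The plan allows a first-order autoregressive mixed model for secondary outcomes. Simplified to equal variances, with T2 observed and T3 missing, it predicts T3 as ρ times the T2 deviation. The bias is then multiplied by (1 − ρf), where f is the part of the gap already visible at T2. With assumed ρ = 0.6 and f = 0.5 the factor is 0.7:

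- 1 exit, G = 1.0: 0.029 × 0.7 = 0.020 SD
- 2 exits, G = 1.5: 0.086 × 0.7 = 0.060 SD

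For 2 exits and G = 1.5, the range over ρ from 0.4 to 0.8 and f from 0 to 1 is 0.017 SD (ρ = 0.8, f = 1) to 0.086 SD (f = 0). For comparison, the standard error of an unadjusted mean difference with 35 per arm is √(2/35) = 0.24 SD, so even 0.086 is about a third of it. The planned missing-not-at-random imputation is not modelled.

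**The case against.** The best reply is that the document already answers the question. The follow-up statement under Missing values covers all patients, gives its reason and makes no exception. The T5 statements are equally unqualified. Termination language is used for responders who are plainly still assessed, so in this protocol it need not mean the end of data collection. The stopping rule names a status and nowhere says that assessments cease. This largely stands. A reader might infer that the protocol contradicts itself, or that nothing in it settles what happens to these children. The text does not support either inference: the weight of the wording favours continued follow-up. What remains is that the rule staff would apply does not say this, and taken at its word points the other way.

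A second reply is that the well-being qualifier in (iv) may govern inpatient need too, so that ending participation is deliberate. The grammar allows that. The remedy therefore keeps a welfare exit, and (v) is the clearer target.

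A third is that an article leaves such detail to the full protocol. That would answer an omission. Here the article states a rule, and the rule works against the principle stated just before it.

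A fourth is that no material effect is shown. This is correct as to size and is reflected in the rating.

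**Conclusion.** The point holds as a minor matter of wording with a practical consequence. The stopping rule gives two clinical reasons for changing treatment the same termination and dropout status as withdrawn consent, and followed literally it would forgo T2 to T5 data that the intention-to-treat principle calls for. Continued follow-up is probably what is meant.

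The loss of data is a risk and not a demonstrated event. It is confined to secondary and supplementary outcomes, and the primary adherence outcome is unaffected. Its size cannot be derived from the document. The SD figures above rest wholly on assumed exit counts, gap, correlation and visibility at T2, and should carry no weight beyond showing that a large effect is unlikely. If exits are balanced between arms in number and severity, the bias in the comparison is zero.

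**What to change.** In the individual stopping rule, state that need for inpatient treatment and reason (v) end the study treatment only. Add that the assessments still due (T2, T3/T4, T5) will be requested unless consent or assent is withdrawn, the family declines, or continued assessment would itself harm the child. Keep study termination for (i) to (iii) and for that welfare ground within (iv). When and why treatment stops does not change.

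The cost is one or two sentences and a little extra contact with a few families, some of them at a difficult time. The assessments are already scheduled and most trial data are collected online.
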